## 4 Treatment Administration and Patient Management

The goal of study treatment is to reach and maintain an HbA1c level  $\leq 6\%$ .

### 4.1 Pre-randomization (Run-in) Period

One component of eligibility screening is a pre-randomization run-in period of up to 6 months but no less than 2 months. The goals of the run-in are to:

- establish a relatively homogeneous study cohort with regard to therapies prior to randomization;

- determine whether potential participants can tolerate metformin within the dose range used in the study;
- ensure that glycemic control can be maintained with metformin alone in a safe range (< 8%) without ketonuria (after withdrawal of other diabetes medications in those participants who were previously treated with them);
- master the standard diabetes education program; and
- assess the ability of the potential participants and their families to adhere to the protocol.

#### 4.1.1 Medical Management

Given that potential participants may be treated with a variety of medication regimens prior to study entry and that metformin is used in all treatment arms, all participants are required to take a minimum of 500 mg of metformin bid in order to be eligible for randomization. During the run-in, metformin naïve participants and participants who are already treated with metformin have metformin initiated and/or doses adjusted according to the recommended titration schedule (table below) with the goal of being able to be treated with 1000 mg bid without side effects and without ketosis. Since all patients are required to take two capsules (consisting of rosiglitazone, metformin, or placebo) twice daily after randomization (see section on masking), patients are required to take two capsules twice a day during the run-in period as well. During the run-in period, the patient is masked to the dose of metformin.

Participants who are already treated with metformin 1000 mg bid need not adjust their doses unless gastrointestinal or other symptoms associated with metformin occur and require dose adjustment.

| Run-in Metformin Titration Schedule (for Metformin Naïve Patients) |                      |                  |                   |                  |
|---------------------------------------------------------------------------|----------------------|------------------|-------------------|------------------|
| Visit                                                              | Pre-breakfast |                  | Pre-dinner |                  |
|                                                                           | Capsule 1     | Capsule 2 | Capsule 1  | Capsule 2 |
| 0                                                                         | placebo              | placebo          | 500 mg            | placebo          |
| 1                                                                         | 500 mg               | placebo          | 500 mg            | placebo          |
| 2                                                                         | 500 mg               | placebo          | 500 mg            | 500 mg           |
| 3                                                                         | 500 mg               | 500 mg           | 500 mg            | 500 mg           |

Baseline and interval HbA1c assays are performed in the central laboratory during the run-in period.

Run-in activities depend on baseline HbA1c as follows:

- If baseline HbA1c < 8% and metformin is already being used in maximal doses (1000 mg bid), no further changes are required.
- If baseline HbA1c < 8% and the participant is not treated with any medication, metformin should be started and increased according to the titration schedule above to achieve the maximum tolerated dose.
- If baseline HbA1c < 8% but the participant is treated with metformin plus other medication(s) such as a sulfonylurea, glitinide, thiazolidinedione, or insulin, metformin should be titrated to maximal tolerated doses and other medications should be tapered and discontinued as glucose levels permit. The schedule for these changes in medications is at the discretion of the investigator.

- If baseline HbA1c  $\geq 8\%$ , the subject should be placed on metformin at maximal tolerated doses and other medications should be weaned with the goal of achieving an HbA1c  $< 8\%$  (checked monthly) and no ketonuria. If glycemic goals are not achieved, insulin should be added but other diabetes medications, such as thiazolidinediones, sulfonylureas, or glitinides, should not be used. Changes in medications are at the discretion of the investigator. Glucose monitoring, at least four times per day while on insulin, and monitoring for ketones should be used to guide medication adjustments and to achieve HbA1c  $< 8\%$ . Once HbA1c is  $< 8\%$ , insulin should be tapered and discontinued as glucose and ketone levels permit. HbA1c must be  $< 8\%$  on metformin alone (at least 500 mg bid) at the time of randomization. The patient must be off other diabetes medications for at least 6 weeks, off TZD for at least 12 weeks, and have no ketonuria.

In summary, the run-in period is between 2 and 6 months. It may be as brief as 2 months if the initial HbA1c is  $< 8\%$  and the participant is either on metformin alone or is started on metformin at the beginning of the run-in. Assuming that metformin (at least 500 mg bid) is tolerated, the standard diabetes education program is mastered, the adherence tasks are completed satisfactorily, and the metabolic goals (HbA1c  $< 8\%$  and no ketonuria) achieved, the participant may be randomized after 2 months if the HbA1c at 2 months is also  $< 8\%$ .

Participants who have had other diabetes medications tapered must be randomized by 6 months. To be eligible for randomization by 6 months, patients must be on metformin alone (at least 500 mg bid), off all other diabetes medications for at least 6 weeks, off TZD for at least 12 weeks, and have HbA1c  $< 8\%$ .

Participants who are not eligible for randomization will be referred back to their primary diabetologist for resumption of on-going care.

#### 4.1.2 Standard Diabetes Education

All patients who are screened for participation in the study receive standard diabetes education (SDE) because SDE is part of the current standard of care for T2DM and because the knowledge and skills imparted are crucial to the patient's ability to follow treatment guidelines in each of the treatment arms.

The purpose of the standard diabetes education (SDE) program is to provide the participants and their parent(s) or guardian(s) with basic knowledge about T2DM and to teach basic survival skills and behaviors that are important for the successful management of this disease. Every patient screened for participation in the study receives the SDE program, which is distinct from the intensive lifestyle intervention that participants randomized to that treatment group receive. As has been shown by multiple studies and meta-analyses [Brown 1990, 1992; Padgett et al. 1988], education is a necessary, but not sufficient, intervention to enhance self-care in people with diabetes. Currently, there are no studies of educational programs for youth with T2DM in the literature. The SDE program is based on the extensive literature on T2DM education in adults and T1DM education in children and youth.

Program materials are provided in a workbook format that is easy to read and culturally appropriate. After each session, mastery activities are included. A participant who does not demonstrate mastery initially is provided with a different subset of questions of equivalent difficulty to assess mastery. Material can be reviewed in person, via telemedicine, or on the phone by the team certified diabetes educator (CDE) concurrently with pre-randomization

study visits. Content is based on the recommendations for nutrition, activity, blood glucose monitoring, and medications that are standard for all groups.

The education program during the pre-randomization period consists of a minimum of six sessions, each lasting 60-90 minutes. Major topics include what diabetes is, nutrition, medications, monitoring, and physical activity:

- *T2DM and its treatment*: medications (what they do and how to take them) and simple logs for keeping track of blood sugar on a twice-daily basis.
- *Weight management*: reviewing food logs and understanding how high calorie drinks and foods, especially fast foods, work against weight management. Portion control, healthier choices, and shopping for healthier foods are all discussed.
- *Physical activity*: understanding how activity helps with weight and blood sugar control, discussing potential areas for increasing activity, and understanding hypoglycemia and its relationship to activity.
- *Living with diabetes*: introduces the concept of setting achievable goals and working toward them.

#### 4.1.3 Demonstration of Adherence

Prior to randomization, all patients also need to demonstrate the ability to adhere to the study assessments and interventions. Clinic attendance and completion of a basic set of behavioral tasks during the eligibility assessment phase demonstrate the willingness and ability of potential participants to adhere to the regimen of study assessments and interventions.

During the run-in period, while diabetes medications (including metformin) are adjusted, the clinic staff assesses the ability of the participants and their families to adhere to the protocol. Satisfactory completion of behavioral tasks, including the performance of self-glucose monitoring, medication taking, keeping a glucose diary and nutrition and activity logs, and attending scheduled visits, are examined by the clinic staff for a period of two months.

Adherence to the treatment regimen specified under the section on medical management, including self-monitoring of blood glucose, is measured. Adherence to metformin is measured by pill counts at all visits. Adherence with scheduled blood glucose monitoring is assessed by downloading the glucose meter. In addition, the patient is asked to keep nutrition and activity records during the eligibility assessment phase that are reviewed and assessed prior to randomization.

## 4.2 Post-randomization Period

### 4.2.1 Medical Management

In order to be eligible for the study, all patients must have an HbA1c < 8%, tolerate at least 500 mg and at most 1000 mg metformin bid, and take no other diabetes medications. Eligible patients are randomized to one of three treatment groups: (1) metformin alone, (2) metformin plus rosiglitazone, or (3) metformin plus intensive lifestyle intervention.

#### 4.2.1.1 Metformin

Metformin use is the same in all treatment groups. Namely, patients remain on the maximum tolerated dose of metformin from 500 up to 1000 mg bid throughout the study.

#### 4.2.1.2 Rosiglitazone

Patients who are randomized to metformin plus rosiglitazone treatment group are started on a dose of 2 mg rosiglitazone bid. After 8 weeks, the dose is increased to 4 mg bid. Patients who reach the primary endpoint and begin add-on insulin therapy (see section 4.7) have the rosiglitazone dose lowered to 2 mg bid.

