#### 4.7 Add-on Insulin Therapy

- *Failure to maintain adequate metabolic control:* If HbA1c  $\geq$  8.0%, therapy is re-invigorated by more frequent telephone contact and visits. If HbA1c remains  $\geq$  8% throughout the next six months, then the patient is classified as failing to maintain

adequate metabolic control and *if* the participant's fasting blood glucose values are not in target then add-on therapy with insulin is initiated.

- *Outcome assessments before the initiation of add-on insulin therapy:* Before starting insulin treatment, participants undergo a comprehensive outcomes assessment unless this has been completed within the past three months.
- *Add-on insulin treatment regimen:* Patients who meet criteria for add-on insulin therapy continue to take the study drug metformin but discontinue the study drug rosiglitazone. The patients and clinicians remain masked to the treatment assignment but are unmasked to HbA1c. Initial insulin treatment is glargine insulin, 0.2 units per kilogram given in the evening. The dose is increased up to 1.0 U/kg/day (to a maximum of 100 units), until fasting blood glucose (FBG) values between 70-150 mg/dL are achieved.  
Add-on glargine insulin therapy is considered unsuccessful if (1) 1.0 U/kg/day (to a maximum of 100 units) does not bring FBG to target within 1 month or (2) HbA1c > 8% at 3 months or (3) HbA1c > 7% at 6 months. At that point, insulin therapy—including adding rapid, short, or intermediate acting insulin—is provided at the clinician's discretion.
- *Self-monitoring of blood glucose (SMBG):* During insulin therapy, patients are asked to monitor blood glucose levels at least four times a day. Target fasting glucose and pre-meal glucose is 70-150 mg/dL and the target peak postprandial glucose is  $\leq 200$  mg/dL.

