## 8.2 Statistical Analysis

The principal analyses of primary and secondary outcomes employ the "intent-to-treat" approach [Peduzzi et al. 1993]. The intent-to-treat analyses include all randomized patients with all patients included in their randomly assigned treatment group; treatment group assignment is not altered based on the patient's adherence to the assigned treatment regimen. All statistical tests are two-sided with the overall significance level of the primary outcome  $\alpha$

$\alpha = 0.05$ . However, b

TODAY, the significance levels used in the interim and final analyses of the primary outcome are adjusted to account for the multiplicity of interim analyses.

- *Baseline characteristics:* Comparison of the baseline characteristics among the three treatment groups uses standard nonparametric statistical techniques, such as Fisher's exact test for categorical data and the Kruskal-Wallis test for ordinal or continuous data.
- *Primary outcome:* The principal analysis of TODAY is an analysis of the time to treatment failure. Turnbull's [1976] algorithm is used to calculate and compare Peto's [1973] nonparametric estimates of the interval-censored survival curves for each treatment group. For the primary outcome analysis, patients are considered "administratively censored" if they complete the full duration of TODAY without having failed. Patients who prematurely discontinue their follow-up visits without having reached study endpoint are "censored" as of their last follow-up visit. Failure is considered to have occurred during the interval between the last HbA1c value  $< 8\%$  and the first HbA1c value used to classify the participant as a treatment failure.
- *Secondary outcomes:* Secondary time to "event" outcomes (e.g., cardiovascular risk factors, microvascular outcomes) are analyzed using the same life-table methods described above for the primary outcome. A proportional-hazards regression model is used to evaluate potential covariates that may modify the primary and secondary time to

event outcomes (e.g., risk population defined by race/ethnicity, age, clinical site). Graphical procedures are used to assess the proportionality assumption. If the proportionality assumption is found to be unreasonable, then other models such as the accelerated failure time model [Wei 1992] or the proportional odds model [McCullagh 1980] are used to evaluate the covariates.

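### Sections 4.2.1.2 and 4.7 give incompatible rosiglitazone instructions for participants who reach the primary endpoint and start add-on insulin: one lowers the dose, the other stops the drug

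*Protocol*

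**What the plan says.** Protocol section 4.2.1.2 (Rosiglitazone) sets the dosing for the metformin plus rosiglitazone arm. Participants start at 2 mg bid, and then "After 8 weeks, the dose is increased to 4 mg bid". The section ends with the rule at failure: "Patients who reach the primary endpoint and begin add-on insulin therapy (see section 4.7) have the rosiglitazone dose lowered to 2 mg bid".

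Section 4.7 (Add-on Insulin Therapy) describes the regimen once insulin is added: "Patients who meet criteria for add-on insulin therapy continue to take the study drug metformin but discontinue the study drug rosiglitazone". It continues: "The patients and clinicians remain masked to the treatment assignment but are unmasked to HbA1c".

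Section 4.7 also sets a condition beyond treatment failure. Failure to maintain control leads to insulin only if the participant's "fasting blood glucose values are not in target then add-on therapy with insulin is initiated". A comprehensive outcomes assessment comes before insulin, unless one was completed in the preceding three months.

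Section 4.3 (Masking) has a table that is said to show all possible combinations of study medication. Every row for the metformin plus rosiglitazone arm contains rosiglitazone, at 4 or 8 mg per day.

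**The concern.** Two operative sections give different instructions for the same drug, in the same participants, at the same point in their care. A reader of 4.2.1.2 who follows its pointer to 4.7 for details of insulin therapy meets the opposite instruction.

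Section 1.3.4 lists fluid retention and edema, congestive heart failure, anemia and weight gain among the known side effects of the class. Comparing the safety of the arms is the first secondary aim in section 1.1. Whether rosiglitazone continues alongside insulin is therefore a safety matter and should not be left open.

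There is also a question of interpretation. Under the intention-to-treat approach of section 8.2, later measurements are compared by randomized arm whatever happens after failure. Such a comparison estimates the effect of a treatment policy, and here the policy after failure is written in two ways. Because patients and clinicians stay masked to assignment, clinic staff could not easily see which rule had been applied.

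**Working it through.** No stated figure is at issue and no sample-size or power formula applies. The check is a side-by-side reading, with simple dose arithmetic.

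**1. Same participants, same moment?** Section 4.2.1.2 covers those who reach the primary endpoint and begin add-on insulin. Section 4.7 covers those who meet the criteria for add-on insulin. In the rosiglitazone arm these are the same people at the same transition. Neither sentence is limited to a subgroup or a period, and neither is said to prevail.

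**2. Can both be followed in sequence?** One might try to read 4.7 as acting when the criteria are met and 4.2.1.2 as acting when insulin starts. That fails: a drug already stopped has no dose to lower, and nothing describes restarting it. The sentence in 4.7 sits in the item that sets out the ongoing add-on regimen, so it is not a temporary hold.

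**3. Dose per day, from the protocol's own figures.**

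| Stage | Rule | Rosiglitazone per day |
|---|---|---|
| Before the endpoint, after week 8 (no safety reduction) | 4 mg bid | 2 × 4 = 8 mg |
| On add-on insulin, section 4.2.1.2 | 2 mg bid | 2 × 2 = 4 mg |
| On add-on insulin, section 4.7 | discontinued | 0 mg |

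The two rules differ by 4 − 0 = 4 mg/day for as long as the participant stays on insulin.

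**4. Does the capsule table decide it?** No. It has rosiglitazone-arm rows at 4 mg/day and none at 0 mg/day. That is not evidence of intent, because the table omits another case the protocol requires. The liver procedure in section 6.2.4 (item B.8) has rosiglitazone permanently stopped while metformin resumes, and that also needs a metformin-only combination in this arm. The table is incomplete on this point whichever rule was meant.

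**5. Which data fall before the conflict and which after?**
- *Before:* the primary outcome. Section 8.2 says "The principal analysis of TODAY is an analysis of the time to treatment failure", and failure comes before add-on insulin. The outcomes assessment that section 4.7 requires ahead of insulin, and the primary-endpoint DXA in section 2.2.4, also belong to this stage.
- *After:* edema, weight and hemoglobin recorded on insulin (sections 2.2.2 and 5.1), end-of-study DXA, any 24-month DXA that falls after insulin has started, and the final-year echocardiogram (section 2.2.10).

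**6. How many participants?** The protocol gives no count of insulin starters. Three relations bound it: insulin starters in the arm ≤ treatment failures in the arm ≤ 250, the planned arm size. The first inequality reflects the fasting-glucose condition in section 4.7. Participants already permanently off rosiglitazone under section 6.2.4 are also outside the conflict.

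**The case against.** The strongest reply is that the contradiction may never have reached a participant. Section 1 places detailed procedures in the manual of procedures, which is not at hand. Section 6.3 has assignments held by the coordinating center, the Drug Distribution Center and, if used, a center pharmacy. Section 9.1 has the distribution center work with the coordinating center on the dosage scheme. One rule, applied centrally, is at least as plausible as divergence between sites. This stands as far as it goes: the documents do not show that participants were treated differently, nor that a consistent masked supply was impossible. It does not remove the defect, because the protocol still gives two incompatible instructions.

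A reader might infer more than the text supports in four ways:

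- *That every rosiglitazone participant who reaches the endpoint is affected.* Both sections tie the rule to add-on insulin, and section 4.7 also requires fasting glucose out of target.
- *That the planning rates in section 8.1 give the number affected.* They would give modelled treatment failures, not insulin starters. The result would also shift with the start of the hazard, which section 8.1 places at the first annual visit, and with accrual, which is three years in section 1.2 and four in section 3.1.
- *That the primary result or every post-endpoint comparison is compromised.* The primary outcome and the pre-insulin assessment precede the conflict.
- *That section 4.2.1.2 relies on 4.7 for its dose rule.* The cross-reference follows the mention of add-on insulin and points to where that therapy is described.

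**Conclusion.** The contradiction is real and must be corrected. It applies to rosiglitazone-arm participants who begin add-on insulin while still on rosiglitazone, and the two readings differ by 4 mg/day. Their number is not given and is at most the number of treatment failures in the arm.

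The primary time-to-failure analysis is not affected. What could be affected is the meaning of post-insulin safety data (edema, weight, anemia) and of end-of-study or final-year measures (DXA, echocardiography) in this subgroup. Different exposure between participants is a foreseeable consequence of the wording, not something the documents report.

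The conclusion rests only on the two sentences and on the absence of any text that ranks or limits them. Its priority comes from conflicting drug instructions in a masked pediatric trial, not from any modelled count. No view is taken on which rule is right.

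**What to change.** 1. Reconcile sections 4.2.1.2 and 4.7 to a single rule, decided through the sponsor's clinical and safety process.
2. Make the section 4.3 capsule table and the dispensing instructions agree with that rule, so that every combination the rosiglitazone arm can require has a row.
3. Use the medication-dose data already scheduled in section 5.1 (quarterly, annual, 24 months, primary outcome, end of study) to identify any participant treated under the other wording. Report how many there were beside the post-insulin safety, body-composition and cardiac results. No new data collection is proposed.

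The cost is a wording correction, a matching edit to the table, a memo to the sites and the Drug Distribution Center, and one look-up in existing data. Sample size and the primary analysis do not change.
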